## Abstract

**Background:**

Subarachnoid hemorrhage (SAH) is a neurological disease with a high mortality rate. Several serious complications frequently arise after successful surgery for this condition. Cerebral vasospasm, one such complication, occurs in 50 to 70% of SAH patients. These patients suffer neurological symptoms known as delayed ischemic neurological deficit (DIND); however, the effect of treatment of vasospasm is limited. The major pathogenesis of cerebral vasospasm is the reduction of nitric oxide (NO) and activation of vasoconstrictors. Acupuncture is known to increase the production and activity of vascular endothelial cell-derived NO and improve endothelium-dependent vasodilatation. A preliminary retrospective case study to investigate the ability of acupuncture to prevent the occurrence of cerebral vasospasm has been conducted. However, no randomized, controlled clinical trials have been carried out to evaluate the efficacy of acupuncture for cerebral vasospasm.

**Methods/Design:**

This trial will be a single-center, randomized, placebo-controlled, parallel group, patient-assessor-blinded clinical trial. A total of 80 patients with SAH will be randomized into two groups: a study group given acupuncture, electroacupuncture, and intradermal acupuncture, and a control group given mock transcutaneous electrical nerve stimulation and sham intradermal acupuncture. Intervention will start within 96 h after SAH, and a total of 12 sessions will be performed during a 2-week period. The primary outcome measure will be the occurrence of DIND, and the secondary outcomes will be vasospasm as measured by cerebral angiography, transcranial Doppler, clinical symptoms, vasospasm-related infarcts, NO and endothelin-1 plasma levels, mortality, and modified Rankin Scale scores.

**Discussion:**

This trial will examine the efficacy and safety of acupuncture for cerebral vasospasm after SAH. The placebo effect will be excluded and the mechanism of action of the treatments will be evaluated through blood testing.

**Trial registration:**

ClinicalTrials.gov NCT02275949, Registration date: 26 October 2014.

## Background

Subarachnoid hemorrhage (SAH) can occur spontaneously or as a result of trauma [1]. The most common cause of spontaneous SAH is aneurysm rupture (about 80% of cases), while vascular malformations, tumors, venous angioma, or infectious aneurysms may also cause bleeding [2,3]. The incidence rate is about 1 per 10,000 people per year, and SAH accounts for about 5% of stroke patients [3,4]. The rate of SAH is low when compared to cerebral hemorrhage or cerebral infarction; however, this condition is a large burden to both individual patients and society because of high mortality rates and treatment costs in neurological intensive care units [5-7].

Treatment of SAH involves early ligation of the aneurysm or insertion of a coil; however, complications such as cerebral vasospasm, rebleeding, or hydrocephalus frequently occur after successful surgery [2-4,7,8]. Such complications increase the mortality rate of SAH or lead to patient sequelae [4]. In particular, cerebral vasospasm is the most serious complication of SAH [9]. It is reported that 23% of the deaths or disabilities that occur as a result of SAH are due to vasospasm [10]. Cerebral vasospasm begins 3 to 4 days after the onset of SAH and reaches a maximum between 7 and 10 days [7,11,12]. Vasospasm occurs in 50 to 70% of SAH patients, and about 50% of these patients suffer neurological symptoms such as deterioration of consciousness and language disorders [3,11,13]. Such symptoms are known as delayed ischemic neurological deficit (DIND). Cerebral infarction occurs in half of DIND patients and a permanent neurological deficit remains in about 35%. In addition, 30% of patients die of DIND [4,7].

Spontaneous vasoconstriction and vasodilatation are adjusted by the physiological regulation of vascular endothelial cells [14]. If a cerebral aneurysm ruptures and cerebral blood flow enters the subarachnoid space, hemoglobin in the blood increases the production of reactive oxygen species (ROS) [15]. This triggers secretion of the vasoconstrictor substances endothelin-1, prostaglandin H2, and thromboxane A2 from vascular endothelial cells and decreases levels of the vasodilatory substance nitric oxide (NO) [6,9,10,15,16]. It is known that cerebral vasospasm occurs via this mechanism. In particular, NO and hemoglobin combine very easily; thus, the presence of hemoglobin results in the loss of vasodilatory function [16]. To prevent vasospasm on the basis of its pathogenesis, various methods such as calcium channel blockers, magnesium sulfate, statin agents, endothelin antagonists, and nicardipine prolonged release implants have been used [2,3,7]. However, their effects are limited and various studies of new drugs and treatments are now under way [4,9,10].

Acupuncture is an effective and safe treatment method that has been used for the treatment of acute stroke including SAH for centuries [17]. In recent years, a number of studies have been published that show that acupuncture increases the production and activity of vascular endothelial cell-derived NO and can improve the function of damaged vascular endothelial cells [18,19]. Acupuncture point ST36 (Zusanli) is known to lower blood pressure and sympathetic nervous tension [18,19]. In particular, it was reported that electroacupuncture stimulation at ST36 lowers blood pressure by increasing the activity of endothelial NO [19]. NO released from endothelial cells plays a key role in maintaining the tension of the vascular wall [20]. Since reduction of NO is the major pathogenesis of cerebral vasospasm after SAH, it can be assumed that acupuncture at ST36 will stimulate the production of NO and normalize endothelial function in patients with SAH. Another acupoint, PC6 (Neiguan), is known to reduce the ischemic heart damage caused by increased myocardial oxygen demand as a result of sympathetic nervous excitement; it also lowers blood pressure and reduces nausea and vomiting [21]. In a study using a finger photoplethysmogram, acupuncture at PC6 was reported to be effective in reducing arterial stiffness in hypertensive patients [22]. Although this study was performed to investigate the acute reaction to acupuncture, it can be assumed that acupuncture at PC6 normalized endothelial cell function and so reduced arterial stiffness.

Based on previous reports, a clinical study was conducted in hypertensive patients with damaged arterial endothelial cell function, which confirmed that acupuncture at ST36-PC6 improved endothelium-dependent vasodilatation [23]. After this, we carried out a preliminary retrospective case study in patients with SAH. The results indicated the possibility of acupuncture treatment in preventing the occurrence of cerebral vasospasm after SAH [24]. To confirm the effectiveness and clinical application of acupuncture for cerebral vasospasm, rigorous clinical trials such as randomized, double-blind trials are required. The aim of this study will be to assess the efficacy and safety of acupuncture treatments in SAH patients for preventing delayed cerebral vasospasm through a randomized controlled trial.

## Methods

This study will be a single-center, randomized, placebo-controlled, parallel group, patient-assessor-blinded clinical trial. The study will be conducted at Kyung Hee University Hospital in Gangdong, Seoul, Korea.

### Ethics

The trial will be carried out in accordance with the Declaration of Helsinki and the Korean Good Clinical Practice Guidelines and has been approved by the ethical committee of the Kyung Hee University Hospital at Gangdong (KHNMC-OH-IRB 2014-001-002). It has been registered on www.clinicaltrials.gov (NCT02275949) and will be reported in compliance with the CONSORT statement (www.consort-statement.org).

### Participants

#### Subject enrollment, randomization, and blinding

A total of 80 participants will be recruited for this trial. Patients with SAH admitted to our hospital are potential candidates for the study. Eligible participants will be randomized to the study group or the control group after written informed consent is obtained. Concealed allocation will be achieved by randomization and allocation by an assigned researcher without patient contact. Randomization will be done using a computer-generated allocation list by an assigned researcher not involved in the intervention or assessment. Stratified block randomization will be carried out according to sex and the Hunt and Hess Scale (HHS) [25]. The physician involved in the intervention will receive a random number by phone after the informed consent form has been signed and the HHS has been evaluated. A flow chart of the study is presented in Figure 1.

**Figure 1 Fig1:**
[figure not shown]
**The flow chart.** HHS, the Hunt and Hess Scale; FG, the Fisher grade; mRS, modified Rankin Scale; NO, nitric oxide; DIND, delayed ischemic neurological deficit.

The participants and the outcome assessors will be blinded to the type of intervention used. The practitioner will not provide any clues about the allocation information to the participants during the study. Blinding will be maintained until the study is completed.

#### Inclusion criteria

Participants conforming to all the following conditions will be included: (1) SAH verified by computed tomography (CT) and cerebral angiography; (2) aneurysm treated by endovascular coiling or surgical clipping; (3) age > 18 years; (4) HHS 1 to 4; (5) acupuncture treatment can start within 96 h after SAH; and (6) participation is voluntary and the informed consent form is signed.

#### Exclusion criteria

Participants with any of the following conditions will be excluded: 1) traumatic or infectious SAH; 2) HHS 5; 3) transcranial Doppler (TCD) cannot be performed; 4) heart, liver, or renal failure; 5) presence of cardiac pacemaker; or 6) have experience of electro-acupuncture.

### Intervention

Intervention will start within 96 h of SAH, after ruptured aneurysms have been secured by endovascular coiling or surgical clipping. Interventions will be applied once a day, 6 days a week for 2 weeks (a total of 12 sessions) in addition to standard treatments such as prophylactic hypertensive, hypervolemic, and hemodilution (triple-H) therapy and nimodipine. Sterile disposable stainless steel acupuncture needles (length, 4 cm; diameter, 0.25 mm) will be used. All interventions will be performed by one Korean Medicine doctor with over 3 years of working experience who completed a college education of 6 years. This doctor will be trained in the study protocol before the start of the trial.

#### Study group

Acupuncture, electroacupuncture, and intradermal acupuncture will be performed at every session. Acupuncture needles (Dong Bang Acupuncture Inc., Chungnam, Korea) will be inserted bilaterally at the acupuncture points Zusanli (ST36), Neiguan (PC6), Gongsun (SP4), and Xiangu (ST43). After insertion to a depth of approximately 1.5 cm, the needles will be manually stimulated until *de qi* (a subjective experience in which patients feel a radiating sensation considered indicative of effective needling) is achieved.

An electric stimulator (ES-160, ITO Co., Japan) will be connected to the handle of each needle in the ST36 and PC6 positions and a current of 5 Hz applied. The current intensity will be increased until light muscle contraction is evident and reaches approximately 70% of bearable intensity. The needles will be left in place for 20 min and then removed. The practitioner will be able to regulate the intensity in response to requests from the subjects.

After the needles are removed, intradermal acupuncture needles with tape (DB130A, 0.25 mm × 1.5 mm, Dong Bang Acupuncture Inc., Chungnam, Korea) will be inserted bilaterally in the ST36, PC6, SP4, and ST43 positions and maintained until the next session.

#### Control group

Mock transcutaneous electrical nerve stimulation and sham intradermal acupuncture will be carried out by the same Korean Medicine doctor. After an electrical insulator (Medi trace 200 foam electrodes, Ludlow Technical Products Canada, Ltd., Ontario, Canada) is attached bilaterally in the ST36 and PC6 positions, the same electric stimulator will be connected to the same points as used in the study group, but without application of current. The subjects in the control group will see the same lights and hear the same sounds coming from the machine as the study group. After 20 min, the electrical insulator will be removed and sham intradermal acupuncture will be performed at the same points. 3 M micropore medical tape (1 cm × 1 cm) will be placed on the skin. After intradermal acupuncture needles are placed over the tape but not penetrating the skin, micropore medical tape of the same size will be placed over the needles. This will remain in place until the next session.

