### Outcome measures

#### Primary outcome measurement

The occurrence of DIND will be compared between the study group and the control group. DIND is defined as an unaccountable new focal neurological deficit lasting ≥2 h. Any occurrence of DIND will be recorded by the physician and verified by the investigator every day.

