## Discussion

In this randomized controlled trial, we aim to observe the effect of acupuncture treatment on the prevention of vasospasm after SAH. In addition to the occurrence of DIND and vasospasm, plasma levels of NO and endothelin-1 will be evaluated to identify the mechanism of action of the treatments used. Stratified block randomization will be used according to sex and severity (HHS). For the placebo control, we will use an electric stimulator without electrical flow and sham intradermal acupuncture designed not to penetrate the skin. With use of the same electrical stimulator and intradermal acupuncture method as the treatment group, better blinding of the control group is expected. Participants will be treated alone in a treatment room in order to avoid any communication with other participants.

In summary, the effect of acupuncture treatment on the prevention of vasospasm after SAH will be assessed in this trial. The placebo effect should be excluded and the trial design should allow for evaluation of the efficacy and safety of acupuncture for SAH patients.

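### The mock control does not support the claim that the placebo effect is excluded, and blinded recording of the primary outcome (DIND) is not secured

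*Protocol article*

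**What the plan says.** **The two procedures.** Under Study group, needles go in on both sides at four acupoints (eight needles) to about 1.5 cm. They are stimulated to de qi, described as "a subjective experience in which patients feel a radiating sensation considered indicative of effective needling". At ST36 and PC6 a 5 Hz current is added: "The current intensity will be increased until light muscle contraction is evident". Penetrating intradermal needles are then taped in place until the next session.

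Under Control group, insulating foam electrodes are attached at ST36 and PC6, and "the same electric stimulator will be connected to the same points as used in the study group, but without application of current". After 20 minutes intradermal needles are laid on tape, without piercing the skin, covered with more tape and left until the next session. Lights and sounds are the same in both arms.

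**The claim.** The Discussion paragraph of the abstract says "The placebo effect will be excluded". The closing Discussion says "The placebo effect should be excluded".

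**Who sees the outcome.** The section on enrollment, randomization and blinding says that participants and outcome assessors are blinded. Assessment says that a blinded investigator evaluates each assessment scale. Primary outcome measurement says: "Any occurrence of DIND will be recorded by the physician and verified by the investigator every day". The only other physician in the article appears in the enrollment section: "The physician involved in the intervention will receive a random number by phone".

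**The concern.** Two separate things are at stake.

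The first is what the trial may conclude. A placebo effect is excluded by design only if the control reproduces everything about the treatment except its presumed active part. Here the most noticeable parts of the treatment are missing from the control. A positive result would be a difference between two packages, and the non-specific effects of being needled and of feeling something would be part of that difference.

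The second is bias in the primary outcome. DIND rests partly on bedside judgement of a new focal deficit. If the person who first notes it knows the arm, doubtful deficits may be noted less readily in acupuncture patients. A later check by a blinded investigator protects against false entries. It protects less clearly against entries that were never made. Under Assessment a neurological change is also one of the two triggers for angiography, so who notices a change can affect how angiographic vasospasm is found.

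**Working it through.** The plan gives no figure for this point, and the stated sample size does not enter it. The main check sets the sections side by side.

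**Step 1. Treatment against control (Study group, Control group).**

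| Element | Study arm | Control arm |
|---|---|---|
| Needles inserted about 1.5 cm, four points, both sides | yes | no |
| Manual stimulation to de qi | yes | no |
| 5 Hz current at ST36 and PC6 | yes | no |
| Light muscle contraction | yes | no |
| Intradermal needles piercing the skin | yes | no, laid over tape |
| Same stimulator at ST36 and PC6 | yes | yes |
| 20-minute session | yes | yes |
| Same lights and sounds | yes | yes |
| Taped intradermal needles kept until next session | yes | yes |

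Five elements differ, and most of them can be felt by the patient. The control is mock TENS with sham intradermal needles. It is not sham needling. The closing Discussion expects better blinding because the stimulator and the intradermal method are the same in both arms. The stimulator is, but the intradermal method differs in skin penetration.

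**Step 2. Route of a DIND event (Primary outcome measurement, Assessment, enrollment section).** A physician records, then the investigator verifies daily. The blinding of the recording physician is not stated. The sentence in Assessment about a blinded investigator refers to assessment scales, and DIND is not a scale. The general statement that outcome assessors are blinded does not say whether the recorder counts as one. As worded, verification starts from a recorded event, so a deficit not recorded has no clear route to the investigator.

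**Step 3. How much unrecorded events could matter (illustration).**

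Inputs: 80 patients in total, so 40 per arm; control DIND rate 38.9% and study rate 10% (Sample size estimation); two-sided 5% level. At the planning rates the expected events are 40 × 0.389 = 15.6 and 40 × 0.10 = 4.0, about 20 in all, so a few events carry weight.

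Assumptions not in the documents: no true effect, with a rate of 38.9% in both arms, and a share *m* of study-arm events never recorded. The recorded study rate is 0.389 × (1 − *m*). With *x* control and *y* study events and p̄ = (*x* + *y*)/80, the uncorrected chi-square test rejects when

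|*x* − *y*|/40 ÷ √(2 p̄(1 − p̄)/40) > 1.96.

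The exact binomial probabilities of all rejecting pairs (*x*, *y*) are summed. The same is done for Fisher's exact test.

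| *m* | Events lost (15.56 × *m*) | Recorded study rate | Apparent benefit (points) | Chi-square rejection | Fisher rejection |
|---|---|---|---|---|---|
| 0 | 0 | 38.9% | 0 | 5.1% | 3.0% |
| 10% | 1.6 | 35.0% | 3.9 | 6.5% | 3.9% |
| 20% | 3.1 | 31.1% | 7.8 | 11.0% | 7.3% |
| 30% | 4.7 | 27.2% | 11.7 | 19.3% | 13.8% |

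Losing three to five events would be enough to double to nearly quadruple the chi-square error rate. Nothing in the documents says that such losses will occur.

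**The case against.** **On the control.** A non-penetrating control is an openly declared design choice, and the Methods/Design paragraph of the abstract describes both packages accurately. Patients see only one procedure, and those with electro-acupuncture experience are excluded. The practitioner gives no clues, and patients are treated alone. Between sessions both arms wear taped needles. A reader might infer that patients will recognise their arm. The documents do not support that: recognition depends on what patients are told, and the consent text is not available here. These safeguards make it harder to identify the arm. They do not make the sensations equal, so the objection to the placebo claim stands.

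**On the recorder.** A reader might infer that the recording physician is the treating doctor and that assessment is therefore unblinded. The text does not show this. The enrollment section qualifies its physician as the one involved in the intervention, while the outcome section has no such qualifier. The person who treats is elsewhere called a Korean Medicine doctor or the practitioner, and a neurosurgeon and a neuroradiologist also appear. Outcome assessors are said to be blinded. This objection stands as far as it goes: broken blinding is not shown. The recorder's status is still unstated.

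**On the route of bias.** Transcranial Doppler runs every other day whatever has been recorded, and the DIND definition under Assessment requires angiographic or Doppler findings. That limits the effect of expectation. But Doppler does not detect a focal deficit, and the definition under Primary outcome measurement does not carry the imaging requirement. Patient expectation itself probably acts less on DIND than on a self-reported outcome.

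**Conclusion.** The point holds in two limited parts.

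1. The statements that the placebo effect will be or should be excluded are not supported by this control. This follows from the Study group and Control group sections alone and needs no assumption. It concerns the permitted conclusion and does not make the comparison invalid.
2. Blinded ascertainment of DIND is not secured, because the recorder's blinding is unstated and verification need not reach unrecorded events. It would go too far to say that assessment is unblinded.

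The size of any bias is unknown. The range of about 6.5% to 19% for the chi-square false-positive rate rests wholly on the assumed equal 38.9% rates and the assumed 10% to 30% loss in one arm. It shows sensitivity and is not an estimate. The absence of a question asking patients to guess their allocation is not counted here, since an article may leave that to the full protocol.

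**What to change.** (a) In the abstract and the closing Discussion, replace the placebo statements. Say that the trial compares a package of acupuncture, electroacupuncture and intradermal acupuncture with mock TENS plus sham intradermal acupuncture, and that non-specific effects of needling and sensation are not fully controlled.

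(b) Under Primary outcome measurement, have the blinded investigator who is already involved daily ascertain DIND in every patient at the daily check, and not only verify recorded cases. State that nobody who delivers the intervention or knows the allocation may record or decide DIND.

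The cost of (a) is a more modest conclusion. The cost of (b) is a slightly larger daily task for the blinded investigator. Neither changes the treatment, the sample size or the analysis.

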### Assessment

The evaluation of each assessment scale will be performed by an investigator blinded to the assigned group. A baseline assessment will include Fisher grade (FG), HHS, modified Rankin Scale (mRS), NO and endothelin-1 in plasma [26]. The occurrence of delayed ischemic neurological deficit (DIND), TCD vasospasm, angiographic vasospasm and a vasospasm-related cerebral infarction will be monitored during the study period. DIND is defined as an unaccountable new focal neurological deficit lasting >2 hours with either angiography or transcranial Doppler findings [27]. TCD (Transcranial Doppler Sys, 2-channel, DWL, Germany) monitoring will be done by a skilled researcher at a certain time every other day [8]. CT angiography or conventional cerebral angiography will be performed when an abnormal increase in blood flow velocity is shown or any neurological changes occur [4,10]. If necessary, we will check whether vasospasm-related infarction has occurred using CT or magnetic resonance imaging (MRI) [8]. Modified Rankin scale will be measured after 2 weeks, and the follow-up assessment will be conducted 2 weeks after the primary endpoint in order to evaluate mortality and mRS.

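### Angiographic vasospasm and infarct are named as incidences but are sought only on triggered imaging, and one trigger overlaps the primary outcome, DIND

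*Protocol article*

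**What the plan says.** The Secondary outcome measurements section of the protocol article names three vasospasm-related incidences: angiographic vasospasm, TCD vasospasm, and vasospasm-related infarct on CT or MRI. An infarct counts only if it lies in a region of angiographic or TCD vasospasm.

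The Assessment section fixes how each is found:

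- Doppler is scheduled: "monitoring will be done by a skilled researcher at a certain time every other day".
- Angiography is triggered: "CT angiography or conventional cerebral angiography will be performed when an abnormal increase in blood flow velocity is shown or any neurological changes occur".
- Infarct imaging has neither a schedule nor a criterion: "If necessary, we will check whether vasospasm-related infarction has occurred using CT or magnetic resonance imaging (MRI".

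On status at entry, the same section says "A baseline assessment will include Fisher grade (FG), HHS, modified Rankin Scale (mRS), NO and endothelin-1 in plasma"; no vasospasm measure is named. The Inclusion criteria require "SAH verified by computed tomography (CT) and cerebral angiography" and that "acupuncture treatment can start within 96 h after SAH". The only Doppler criterion among the exclusions is feasibility: "transcranial Doppler (TCD) cannot be performed". The Background states that "Cerebral vasospasm begins 3 to 4 days after the onset of SAH". The Statistical analyses section includes all randomized participants.

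**The concern.** An incidence compared between arms is interpretable when both arms are searched equally hard. Here the search depends on events after randomization, and one of these, neurological change, overlaps the primary outcome. If acupuncture lowers DIND by any route, fewer study patients will be sent for angiography on that ground. Vasospasm that causes no symptoms and no Doppler alarm is then never seen, and this happens to more patients in the arm with less DIND. Infarct is filtered twice: a scan has to be judged necessary, and the lesion has to match vasospasm that was itself detected.

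At stake is how the secondary results are read. The trial aims to show prevention of vasospasm, and a lower rate of angiographic vasospasm or infarct would look like independent support for the DIND result when it may partly repeat it. Blinded assessment does not cure this, because the imbalance arises from who is imaged and not from how the images are read.

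A second, smaller matter is timing. Treatment may start as late as day 4, when by the Background vasospasm may already have begun, and no vasospasm status at entry is specified.

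**Working it through.** The plan gives no figure for this point, so there is none to reproduce. The check is an illustration of how large the artefact could be.

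**Inputs from the protocol**

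- DIND rates from Sample size estimation: control 38.9%, study 10%. Difference 38.9 − 10 = 28.9 points, as stated there.
- Vasospasm frequency from the Background: 50 to 70%. The midpoint, V = 60%, is used in both arms, so there is no true effect on vessel calibre.
- 80 patients in total, hence 40 per arm.

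**Assumptions not in the protocol**

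- Every DIND patient has vasospasm and is imaged.
- A share s of vasospasm without DIND is picked up by the Doppler trigger, the same share in both arms. The protocol gives no value; s is varied from 0.3 to 1.
- Patients not imaged are counted as having no event. The protocol does not state this; it is what an incidence over all randomized participants implies.

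**Formula**

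Detected incidence = D + (V − D) × s, where D is the DIND rate in the arm.

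| s | Control | Study | False gap |
|---|---|---|---|
| 0.3 | 0.389 + 0.211 × 0.3 = 45.2% | 0.10 + 0.50 × 0.3 = 25.0% | 20.2 points |
| 0.5 | 0.389 + 0.211 × 0.5 = 49.4% | 0.10 + 0.50 × 0.5 = 35.0% | 14.4 points |
| 0.7 | 0.389 + 0.211 × 0.7 = 53.7% | 0.10 + 0.50 × 0.7 = 45.0% | 8.7 points |
| 0.9 | 0.389 + 0.211 × 0.9 = 57.9% | 0.10 + 0.50 × 0.9 = 55.0% | 2.9 points |
| 1.0 | 60.0% | 60.0% | 0 |

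Subtracting the two arms gives gap = (1 − s) × (38.9 − 10) = (1 − s) × 28.9 points. V cancels, so the gap is the same at 50% or 70%. It shrinks in proportion if the true DIND difference is smaller than planned.

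With 40 per arm and the usual normal approximation, the chance of a nominally significant result favouring acupuncture is about 47%, 26%, 12% and 4.5% for s = 0.3, 0.5, 0.7 and 0.9. Without the artefact it would be 2.5%.

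**Vasospasm already present at entry**

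Suppose a fraction b of both arms has vasospasm before the first session and is counted as an event. A rate p becomes b + (1 − b) × p, and a true difference is multiplied by (1 − b). Taking 28.9 points as the example, b = 10%, 20% or 30% (assumed) leaves 26.0, 23.1 or 20.2 points. On average this effect pulls toward no difference.

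**The case against.** The strongest answer is the Doppler schedule. Every participant must be able to have TCD, the readings are made every other day without regard to arm, and an abnormal velocity alone leads to angiography. This is universal screening followed by confirmation, and fewer Doppler alarms in one arm is real evidence about the vessels. That stands, so a reader who infers that detection depends on symptoms alone goes further than the text allows. What remains is vasospasm without symptoms that Doppler misses. The Assessment section sets no threshold for an abnormal increase, and the TCD outcome is defined on the middle cerebral artery only. Infarct imaging has no such scheduled trigger.

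It is also fair that the article does not say how patients without imaging enter the analysis; that may be settled in a document not shown. The point does not need such a rule to be written down. Counting them as event-free gives the gap above, and restricting the analysis to imaged patients would select on a post-randomization event.

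On baseline, a reader might infer that no image of the vessels exists at entry, or that cases already present would create a false benefit. Neither is supported. Cerebral angiography is already required to verify SAH, although no reading of it for vasospasm is specified. Randomization spreads cases already present over both arms, so they mainly dilute an effect or add chance imbalance.

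Finally, these are secondary outcomes, and the primary comparison of DIND does not rest on them.

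**Conclusion.** The point holds for the two imaging outcomes. As written, the plan can produce a difference between arms in detected angiographic vasospasm, and in detected infarct, with no difference in vessel calibre, provided DIND differs between arms. For angiographic vasospasm the false gap is (1 − s) × the DIND difference: about 20 to 3 points as s goes from 0.3 to 0.9 at the planning rates, and nil if Doppler catches every silent case. The direction follows from the protocol. The size rests on s, on every DIND patient having vasospasm and being imaged, and on patients without imaging counting as event-free. Infarct is the more exposed outcome, but the documents give nothing from which to put a number on it.

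The documents do not support saying that the trial will reach a false conclusion about prevention: with good Doppler capture the artefact is small. The missing vasospasm status at entry is a lesser point, about dilution and chance imbalance.

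**What to change.** 1. Define both outcomes as angiographic vasospasm, and vasospasm-related infarct, detected on triggered imaging.
2. Report by arm the number of patients imaged and the trigger for each (Doppler, neurological change, other). For infarct, record the reason why the scan was judged necessary.
3. State that these two outcomes will not be read as independent evidence that vasospasm is prevented. Rest that claim on TCD vasospasm, which already has a definition and a fixed schedule for everyone, and note that it speaks for the middle cerebral artery.
4. Record vasospasm status before the first session, either from the entry angiogram that is already required or by placing the first scheduled TCD reading before session 1. Count only vasospasm first seen afterwards.

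This adds no angiography, CT or MRI and leaves clinical decisions on imaging and treatment as they are. The cost is wording, two extra items on the case report form, possibly a shift in the timing of the first Doppler reading, and a narrower secondary claim.
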